#### The intervention group

Participants in the intervention group will be provided with access to the e-bibliotherapy app installed on their smartphones. A standardized bibliotherapy manual will also be distributed to them for convenient reference. The manual, which has been pilot tested, comprises eight chapters, each approximately ten pages in length [19]. Each chapter centers on a single active component that could potentially influence a caregiver’s psychological well-being. The intervention materials from the manual (texts, relevant explanatory images, and assignments), matched with corresponding videos and audio, will be uploaded to the app, and only the intervention group will be granted authorization to access them.

During the intervention, participants will undergo eight weekly sessions of e-bibliotherapy (Table 1). Each session will entail viewing an explanatory video, reading a chapter or listening to the audiobook, and completing the corresponding tasks. This is an individual self-help intervention, enabling caregivers to complete the watching and reading at their convenience, at any time and location. Telephone coaching, if required, can also be availed. The research team will monitor participants’ intervention completion levels through statistical functionality. For those who have completed less than 60% of the tasks or require assistance with problems, standardized protocol-based telephone coaching will be arranged. The coaching aims to enhance participants’ adherence and safety, and will be conducted by a trained research assistant with a background in psychology or nursing. Each coaching session will last for no more than 30 min, as reported by our pilot study. The coaching manual encompasses troubleshooting plans, such as behavior management, caregiver distress, and caregiver discouragement, which are designed to address unforeseen circumstances [19].

**Table 1 Tab1:** Intervention protocol for this study

Weekly tasks	Session	Contents
Watch session 1 videos Read session 1/listen to audiobook session 1 Finish assignment/coaching	Dementia and caregiver health	• What is dementia • Stages and symptoms of dementia
		• Can dementia be cured
		• How providing care can affect you as a caregiver
Watch session 2 videos Read session 2/listen to audiobook session 2 Finish assignment/coaching	Controlling care recipient behavioral problems	• Learning more about behavioral problems
		• Finding the “triggers” for problem behaviors
		• Ways to change care recipient behavioral problems
Watch session 3 videos Read session 3/listen to audiobook session 3 Finish assignment/coaching	Home safety and daily caregiving skills	• How to ensure home safety
		• How to deal with difficulties in daily care
		• Some financial and legal issues in caregiving
Watch session 4 videos Read session 4/listen to audiobook session 4 Finish assignment/coaching	Improving the dyadic relationship	• How to communicate with the care recipient
		• Using non-verbal communication to improve the relationship
		• Increasing pleasant events with the care recipient
Watch session 5 videos Read session 5/listen to audiobook session 5 Finish assignment/coaching	Improving confidence	• The importance of confidence in caregiving
		• How to improve caregiving confidence
		• Some “Basic Rights” of caregivers
Watch session 6 videos Read session 6/listen to audiobook session 6 Finish assignment/coaching	Recognizing and relieving stress	• Danger signals and how to recognize early signs of stress
		• Skills of relaxation and why it is so important for caregivers
		• Using relaxation in stressful caregiving situations
Watch session 7 videos Read session 7/listen to audiobook session 7 Finish assignment/coaching	Recognizing and dealing with depression	• Recognizing common symptoms of depression
		• Depression and its influence
		• How some little daily events can help prevent or reduce depression
Watch session 8 videos Read session 8/listen to audiobook session 8 Finish assignment/coaching	Improving family coping and seeking social support	• Family coping in dementia caregiving
		• Ways to improve family coping
		• How to seek help from relatives and friends
		• How to seek help from professionals

#### The control group

Participants in the control group will utilize the identical e-bibliotherapy application, yet they will only be authorized to access another portal offering general daily living knowledge distinct from the intervention content. They will be requested to complete a session weekly for a duration of eight weeks. Upon project completion, they will gain access to the intervention group’s content.

#### Outcomes

##### Psychological well-being

Psychological well-being will be measured with the Chinese version of Ryff’s Psychological Well-being Scale [27]. It is a 6-point Likert scale with 1 = *strongly disagree* to 6 = *totally agree*. A higher score indicates better psychological well-being. It includes 18 items and is divided into 6 subscales: positive relations with others, autonomy, environmental mastery, personal growth, purpose in life, and self-acceptance. The Cronbach’s α of the whole scale is 0.936, and the αs for the subscales ranged from 0.709 to 0.910 in our pilot study [19].

##### Caregiving appraisal

The Chinese version of the Caregiving Appraisal Scale [28] will be used. It is a 5-point Likert scale, with higher scores indicating more positive caregiving appraisals. It includes 26 items and is divided into 4 subscales: caregiving burden, caregiving satisfaction, caregiving mastery, and caregiving impact. The Cronbach’s α of the whole scale was 0.883, and the αs for the subscales ranged from 0.651 to 0.854 in our pilot study [19].

##### Mental health

The Chinese version of the Depression Anxiety Stress Scale-21 (DASS-21) will be used to measure the mental health problems of the participants. The DASS-21 is a 4-point Likert scale. It includes 21 items with three dimensions: depression, anxiety, and stress. The DASS-21 has demonstrated good reliability among Chinese adults, with Cronbach’s α ranging from 0.80 to 0.83 for each subscale [29].

##### Biomarker of stress

Saliva cortisol concentration will serve as a stress biomarker, as cortisol is the major hormone that reflects stress levels and helps the body cope with stress. It is a sensitive measure of stress among dementia caregivers [30], with morning cortisol levels validly predicting daily stress levels. Therefore, saliva samples will be collected upon waking for cortisol assessment.

##### Health-related quality of life

The 12-item Short Form Survey (SF-12) will be used [31]. The SF-12 is often used to indicate quality of life and as a proxy for health status. According to Lam et al. (2013), the SF-12 represents a valid, reliable, and sensitive measurement among the Hong Kong Chinese population. The Cronbach’s α of the scale is 0.7.

##### Covariates

Demographic data about various aspects of the caregiving situation will be collected at baseline, such as age, gender, kinship, education level, caregiving duration, intensity of care, and the care recipient’s stage of dementia.

#### Participant timeline

The study flowchart is shown in Fig. 1, and the study timeline is shown in Table 2. Participants will be assessed at four time points: baseline (T0), immediately post intervention (T1), 3 months (T2), and six months (T3) post intervention. After receiving consent from the participants, a research assistant who is blinded to the group allocation will conduct the baseline assessment (T0). Each participant will be coded with a subject ID number that is not related to their personal information. Qualtrics will be used to collect survey data. Telephone interview will be used as a contingency plan in case the caregiver requests help in filling out the questionnaires.

Before project initiation, a briefing session will be conducted to train participants on how to use the E-bibliotherapy App and collect and store saliva samples to assess a stress biomarker. This is because the stress response is considered a potential mechanism that can negatively impact psychological well-being [32]. A Salivette® collection device kit (Sarstedt, Nümbrecht, Germany) and a user guide will be distributed to each participant.

**Fig. 1 Fig1:**
[figure not shown]
The CONSORT flowchart

**Table 2 Tab2:** Time schedule of enrolment, interventions, and assessments

	Study Period				
	Enrolment	Allocation	Post-allocation		
Timepoint	-t_0_	t_0_	t_1_	t_2_	t_3_
	***1–9 m***	***1–9 m***	***4–12 m***	***7–15 m***	***10–18 m***
**Enrolment**:					
Eligibility screen	X				
Informed consent	X				
Allocation		X			
**Interventions**:					
E-bibliotherapy group		There is an arrow covering T0 to T2			
Control group		There is an arrow covering T0 to T2			
**Assessments**:					
Psychological well-being (Ryff’s psychological well-being scale)		X	X	X	X
Caregiving appraisal (Caregiving appraisal scale)		X	X	X	X
Mental health (DASS-21)		X	X	X	X
Biomarker of stress (Saliva cortisol concentration)		X	X	X	X
Health related quality of life (SF-12)		X	X	X	X

Note: t_0_: baseline assessment, t_1_: immediately post-intervention, t_2_: 3 months post-intervention, t_3_: 6 months post-intervention

#### Randomization, blinding, and allocation concealment

Stratified randomization will be used to allocate the participants within two weeks after the baseline assessment. Firstly, caregivers will be grouped into two strata, one comprising adult child caregivers and the other consisting of spousal caregivers. In order to ensure a balanced number of different types of caregivers in each group, simple randomization will then be performed with each stratum. The allocation sequence will be generated by the statistician on our research team, and a research assistant who is not involved in data collection will assign participants to their respective groups. The sequence of the participants will remain concealed until group allocation is designated. The data collector and community healthcare professionals will be blinded to the group allocation. Given the nature of the intervention, it will be impossible to blind the participants and the intervention facilitator.

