**Method:**

The study is divided into two phases. In phase 1, the research team will co-design the e-bibliotherapy app with caregivers. In phase 2, a randomized controlled trial will be conducted among 192 informal caregivers of people with dementia in Hong Kong. Caregivers will be randomly assigned to either the e-bibliotherapy group or the control group using simple randomization. Outcome measures will encompass caregivers’ psychological well-being, caregiving appraisal, mental health, saliva cortisol levels as an indicator of stress, and health-related quality of life for caregivers. Data will be collected at baseline, immediately post intervention, and 3 months and 6 months post intervention. General linear mixed model will be employed to analyze intervention effects. Qualitative interviews will be undertaken to explore caregiver experiences within this study and evaluate intervention acceptability using conventional content analysis methods.

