#### Sample size

The sample size was calculated by testing between-and-within interactions in a General Linear Mixed Model (GLMM), using the software “General Linear Mixed Model Power and Sample Size”. Type I and II errors were set at 0.05 and 0.2, respectively. The marginal means of psychological well-being from the pilot study at baseline and post intervention were 84.07 and 86.35, respectively, for the intervention group. For the control group, they were 73.5 and 70.7, respectively. We assume that the follow-up values for the intervention group are equal to 85.7 and 85.2; 71 and 71.3 for the control group. The standard deviation of the pilot study was 13. An autoregressive correlation structure (AR1) with a correlation equal to 0.7 was used. To achieve alpha = 0.05 and power = 0.801, the estimated sample size would be 160. Considering the 20% attrition rate of the pilot study, the estimated sample size would be 192 in total.

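### Simple randomization within the kinship strata cannot guarantee the caregiver-type balance that the protocol says it ensures

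*Protocol article*

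**What the plan says.** The section on randomization, blinding and allocation concealment opens with "Stratified randomization will be used to allocate the participants within two weeks after the baseline assessment". It defines the strata: "caregivers will be grouped into two strata, one comprising adult child caregivers and the other consisting of spousal caregivers". It then gives both the within-stratum method and its purpose: "In order to ensure a balanced number of different types of caregivers in each group, simple randomization will then be performed with each stratum". No block, minimization or other restriction is mentioned there or elsewhere in the article.

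The Method paragraph of the abstract describes the allocation without strata: "Caregivers will be randomly assigned to either the e-bibliotherapy group or the control group using simple randomization".

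The planned number comes from the sample size section: "Considering the 20% attrition rate of the pilot study, the estimated sample size would be 192 in total". The article gives neither the expected number of spouses and adult children nor the allocation ratio.

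**The concern.** Stratification balances a factor only if the allocation is restricted inside each stratum, for example by permuted blocks. If each assignment is an independent draw, it makes no difference whether the draws are listed by stratum or in one sequence. The section therefore names a purpose and a method that does not serve it.

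This is not a detail left to a fuller document. The article names the within-stratum method, and the abstract uses the same term. If a restricted list is intended, the published text is wrong. If the text is meant literally, the design lacks the property claimed for it. A trial report that followed this section would call the allocation stratified and balanced by design when it was neither in effect.

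**Working it through.** **Inputs.** 192 participants (sample size section); two arms (study design section); two kinship strata with simple randomization in each (randomization section).

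**Assumptions.** Allocation is 1:1, every participant falls in one of the two strata, and there are 48, 64 or 96 spouses among the 192. The article states no figure for balance, so there is none to reproduce.

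**Step 1: do the strata change the allocation?** Under simple 1:1 randomization each assignment has probability 1/2, independently of the others. With 48 spouses and 144 adult children, any particular list of assignments has probability (1/2)^48 × (1/2)^144 = (1/2)^192. Without strata the same list also has probability (1/2)^192. The two schemes are identical in distribution, whatever the split.

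**Step 2: imbalance in one stratum.** In a stratum of n, the arm difference is D = 2X − n with X ~ Binomial(n, 0.5), and its standard deviation is √n.

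| Stratum size n | SD of D | P(\|D\| ≥ 10) |
|---|---|---|
| 48 | 6.9 | 19% |
| 64 | 8.0 | 26% |
| 96 | 9.8 | 36% |
| 128 | 11.3 | 43% |

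The chance that at least one of the two strata differs by 10 or more is 56% to 59% over the three splits.

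**Step 3: imbalance in kinship mix.** With spouse proportion p and about 96 per arm, the difference in spouse share has standard deviation of about √(p(1 − p) × 2/96). For p = 0.25, 0.333 and 0.5 this is 0.0625, 0.0680 and 0.0722. A 10-point difference is then 1.60, 1.47 and 1.39 standard deviations, with two-sided probabilities of about 11%, 14% and 17%. Simulation agrees (200,000 draws with strata, 50,000 without):

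| Spouses of 192 | Share differs by > 10 points, as written | Same, no strata |
|---|---|---|
| 48 | 10.6% | 10.7% |
| 64 | 13.9% | 13.7% |
| 96 | 17.0% | 17.2% |

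The last two columns agree within simulation error, as Step 1 requires.

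**Step 4: overall arm sizes.** The SD of the difference is √192 = 13.9, and the chance of a difference of 20 or more is 17%.

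**Step 5: cost in efficiency.** Relative to equal arms, efficiency is 4·n₁·n₂/N² = 1 − D²/N². Since E[D²] = N, the expected loss is 1/192, about 0.5%. At a difference of 20 (106 against 86), efficiency is 4 × 106 × 86/192² = 98.9%.

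**Step 6: with restriction.** In a 1:1 permuted block the running difference never exceeds half the block size: 2 for blocks of 4 and 3 for blocks of 6. With both sizes in use, the cap is 3 per stratum and 6 overall. A difference of 3 spouses between equal arms of 96 is 3/96, or about 3 percentage points in spouse share.

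**The case against.** Simple randomization is a legitimate choice. It is unbiased, fully unpredictable and leaves the type I error intact. The efficiency loss in Step 5 is trivial. A 10-point difference in spouse share shifts the crude contrast by only 0.1 times the kinship effect. For an assumed kinship effect of 0.25 to 1.0 SD, that is 0.025 to 0.10 SD, or about 0.3 to 1.3 points at the pilot SD of 13. This shift is random error, which the standard error already reflects. The sample size rests on a group-by-time interaction, and a constant difference in level between kinship groups cancels from that contrast. Kinship is also collected at baseline under the covariates heading, so an imbalance would be visible and could be adjusted for. Whether it will be may be settled in an analysis plan that is not shown. All of this stands, and it limits how serious the point is. It does not make the sentence about ensuring balance true.

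Four stronger readings are tempting, and the article does not support them:

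- **That balance cannot occur.** It can arise by chance, and under the assumed splits the spouse share stays within 10 points in about 83% to 89% of draws. What is missing is a guarantee.
- **That kinship was judged prognostic.** The article gives balanced numbers as the only reason for stratifying.
- **That the abstract and the methods prescribe different allocations.** By Step 1, as written, they give the same allocation probabilities. The abstract omits the strata, which is a difference of description. It becomes one of substance only once a restriction is added within strata.
- **That the results would be invalid or biased.** Nothing in the article or the arithmetic points that way.

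**Conclusion.** The stated method does not deliver the stated purpose. Simple randomization inside the two kinship strata is the same, in distribution, as no stratification, so balance of caregiver types is not ensured. This conclusion follows from the wording and does not depend on the stratum sizes.

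The size does depend on assumptions. With 1:1 allocation and 48 to 96 spouses of 192, there is an 11% to 17% chance of a difference in spouse share above 10 percentage points.

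Severity is moderate: a design claim needs correcting, while the trial's validity is intact and the expected efficiency loss from unequal arms is about 0.5%.

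**What to change.** For participants not yet randomized, replace simple randomization within strata by restricted 1:1 allocation. One suitable form is permuted blocks of randomly varying size 4 and 6 in each stratum, with block sizes concealed from those who enrol and those who assign. Another restricted method would also serve. State the allocation ratio in the same sentence.

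If simple randomization is kept, delete the claim that it ensures balance and do not present the strata as balancing the arms.

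In either case, align the abstract's Method paragraph with the final scheme.

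The cost is a revised list from the statistician who already generates the sequence, and a sentence in each of two places. The downside of blocking is slightly more predictability. Random block sizes limit it, as do two features already in the article: allocation follows the baseline assessment, and the person who assigns takes no part in data collection. The article anticipated recruitment from May 2024 and does not show whether it has begun. Participants already randomized keep their allocation, and the report should then describe both schemes and the point of change.

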#### Nested qualitative study at T1

A nested qualitative study will be conducted at T1 to explore participants’ experiences using the intervention and facilitate knowledge translation. Focus group interviews will be conducted with participants representing varying intervention completion levels. The interview guide will encompass overall experiences with the intervention, perceived benefits, facilitators, encountered barriers, and suggestions for improvement. Thematic saturation will be used as the criterion for ceasing the data collection.

#### Data analysis

##### Quantitative data analysis

R software will be used for analyses. Descriptive statistics will be used to summarize the baseline data. Independent t-test, Mann-Whitney U test, or chi-square test will be used to compare the baseline data. To evaluate the intervention’s efficacy, GLMM will be used. In all analyses, a significance level of 5% will be used. Cortisol concentrations will be analyzed at a collaborating laboratory using radioimmunoassay.

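### The only efficacy test described lets the arms' baseline means differ; a common baseline mean would cut the variance of the treatment contrast by 15–33% at no cost

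*Protocol article*

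**What the plan says.** Under Quantitative data analysis, the article says that to evaluate "efficacy, GLMM will be used". It lists no model terms there. The one place where the tested effect is described is Sample size: "The sample size was calculated by testing between-and-within interactions in a General Linear Mixed Model (GLMM". That calculation enters psychological well-being at baseline and three later visits, with a different baseline mean in each arm: "at baseline and post intervention were 84.07 and 86.35, respectively, for the intervention group", and "For the control group, they were 73.5 and 70.7, respectively". The Hypothesis section is likewise worded in terms of improvement, at each of the three post-intervention visits.

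Three further statements bear on the point:
- Randomization, blinding, and allocation concealment places allocation after the baseline assessment and stratifies by kinship: "caregivers will be grouped into two strata, one comprising adult child caregivers and the other consisting of spousal caregivers".
- Covariates lists kinship among the variables collected at baseline, without saying which of them enter the model.
- Quantitative data analysis plans significance tests at baseline: "Independent t-test, Mann-Whitney U test, or chi-square test will be used to compare the baseline data".

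**The concern.** In a group-by-time interaction with baseline as a free time point, the treatment effect at each visit is a difference between arms in change from baseline. Both arms' baseline means are estimated from the data, although randomization after baseline makes the true means equal. The cost of ignoring this grows as the correlation with baseline falls. Under the plan's AR(1) that correlation is 0.7 at T1, 0.49 at T2 and 0.343 at T3, so most is lost at the follow-up visits, where the assumed effects are smallest.

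A change contrast also over-corrects a chance baseline gap. Given a gap g, the estimate shifts by −(1 − r)g in expectation: 0.30g at T1, 0.51g at T2 and 0.66g at T3. Randomization here is simple within strata, which does not force balance on the baseline score. The planned baseline tests do not help, because a significance test leaves the effect estimate as it was.

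**Working it through.** **Inputs (Sample size section).** Means at T0, T1, T2, T3 are 84.07, 86.35, 85.7, 85.2 (intervention) and 73.5, 70.7, 71, 71.3 (control). SD σ = 13, AR(1) correlation 0.7, alpha 0.05, stated power 0.801 at N = 160, 192 recruited, 20% attrition. Equal allocation is assumed, because no ratio is given.

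**Effects.** Arm differences are 10.57, 15.65, 14.70 and 13.90. Subtracting the baseline difference gives differences in change δ = 5.08 (T1), 4.13 (T2) and 3.33 (T3).

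**The plan's own figure.** For the 3-df interaction, λ = (N/4) δ′V⁻¹δ, where V is the covariance of the three change scores under σ² × AR(1). At N = 160, λ = 10.23. Power is 0.760 from the noncentral F and 0.772 from the noncentral chi-square, so the stated 0.801 is not reproduced; the F test needs N = 176 to reach it. Constant correlation of 0.7 gives 0.814, but that is not the stated structure.

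**Variance at a single visit.** With correlation r between that visit and baseline:
- free baseline: (4/N) σ² × 2(1 − r)
- common baseline, or baseline as covariate: (4/N) σ² × (1 − r²)
- ratio: (1 + r)/2

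| Visit | r | 2(1 − r) | 1 − r² | Ratio | Variance cut | SE cut |
|---|---|---|---|---|---|---|
| T1 | 0.7 | 0.600 | 0.510 | 0.850 | 15.0% | 8% |
| T2 | 0.49 | 1.020 | 0.760 | 0.745 | 25.5% | 14% |
| T3 | 0.343 | 1.314 | 0.882 | 0.672 | 32.8% | 18% |

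For the average of the three visits the factor falls from 0.731 to 0.492, a cut of 32.7%.

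**Power with the same δ.** For the constrained joint test, V becomes the covariance of T1–T3 given T0. At N = 160, λ rises from 10.23 to 12.22, a factor of 1.19. After attrition, 192 × 0.8 = 153.6, taken as 154.

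| Test (correlation 0.7) | N | Free baseline | Common baseline |
|---|---|---|---|
| Joint, 3 df | 160 | 0.760 | 0.837 |
| Joint, 3 df | 154 | 0.742 | 0.821 |
| Average of T1–T3 | 160 | 0.657 | 0.821 |
| T1 alone | 160 | 0.89 | 0.93 |
| T2 alone | 160 | 0.51 | 0.63 |
| T3 alone | 160 | 0.29 | 0.40 |

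The single-visit figures use the t distribution; a normal approximation gives 0.41 instead of 0.40 for the last entry. With a common baseline, N = 148 is enough for joint power of 0.801.

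**Sensitivity to the correlation (joint test, N = 160).**

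| AR(1) correlation | Free | Common | Variance cut, T1 to T3 |
|---|---|---|---|
| 0.6 | 0.620 | 0.761 | 20% to 39% |
| 0.7 | 0.760 | 0.837 | 15% to 33% |
| 0.8 | 0.919 | 0.942 | 10% to 24% |

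**Kinship stratum.** The documents give no figure for how much variance it explains. If it explained an assumed 0–5%, free-baseline joint power at N = 160 would move only from 0.760 to 0.783. None of the gains above come from it.

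**The case against.** The strongest reply is that the efficacy sentence fixes no baseline handling. A constrained or baseline-adjusted mixed model would fit it equally well, the sizing would then be conservative, and model terms are commonly left to an analysis plan that is not shown. This stands in part: the free-baseline form is read from the sizing text, not stated as the efficacy model. But it is the only test the article describes, the same model is named for efficacy, and the sample size rests on it. The point is therefore a better choice of method and does not depend on missing detail.

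A reader might go further in four ways that the documents do not support:
- *The model leaves out the kinship stratum.* Nothing excludes it, and Covariates names kinship. The article simply does not say whether it is a term.
- *The group-by-time test is invalid.* It is a valid analysis of a randomized trial; the loss is in efficiency.
- *A common baseline restores adequate power throughout.* It does so for the joint test and the average effect at correlation 0.7. It does not for T2 or T3 singly, which the Hypothesis also names, nor for the joint test at correlation 0.6.
- *The pilot's 10.57-point baseline gap shows what to expect.* With 192 caregivers split equally, the standard error of a chance gap is 13 × √(4/192) ≈ 1.9 points, so a gap that size would exceed five standard errors. A gap of one standard error is realistic, and at T3 it would shift the change contrast by about 0.657 × 1.88 ≈ 1.2 points against an assumed effect of 3.33.

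The shortfall below 0.801 also has separate causes: the stated power does not reproduce under AR(1), and 160 × 1.2 = 192 allows too little for 20% attrition. A common baseline offsets that shortfall, but the choice of model did not cause it.

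**Conclusion.** The point holds as a free improvement. Under the plan's own SD and AR(1) 0.7, with equal allocation and its assumed differences in change taken as the treatment effects, a common baseline mean takes 15% (T1) to 33% (T3) off the variance of the treatment contrast. It lifts joint power above the stated 0.801, both at 160 and at about 154 completers. The direction of the gain does not depend on the correlation: (1 + r)/2 is below 1 whenever r is below 1. Its size does, as does whether 0.801 is reached. No numerical gain is claimed for the kinship stratum or for dropping the baseline tests.

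**What to change.** State the efficacy model as a constrained longitudinal mixed model: outcomes at T0–T3, one baseline mean common to both arms, and a treatment effect at each of T1, T2 and T3. Equivalently for this purpose, take T1–T3 as outcomes with baseline score by visit as a covariate. Include the kinship randomization stratum as a fixed effect, and say so. Replace the baseline significance tests with a description of baseline by arm.

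The cost is wording only. Baseline scores and kinship are already collected, the analysis stays a mixed model in R, and no extra caregivers are needed. If separate conclusions at T2 and T3 are intended, this change alone does not provide the power for them.
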